### Eligibility Criteria

2.3

Participants were eligible if they were aged between 45 and 70 years, had a KOA diagnosis as defined by the American College of Rheumatology, had a Kellgren‐Lawrence index of II or III, and signed the informed consent form. Exclusion criteria included systemic inflammatory arthritis; recent oral steroid use within 3 months; recent knee treatment or corticosteroid injections within 6 months; previous knee surgery; neurological deficits; cardiopulmonary conditions that prevent exercise; and contraindications to KT, such as severe skin injuries, open wounds, allergies, and pregnancy [4, 19, 20]. We aim to ensure equal and impartial recruitment.

### Randomization and Blinding

2.4

Participants were randomly assigned in a 1:1 ratio to receive KT with NCE or sham KT with NCE. Randomization was carried out using sequentially numbered, opaque, sealed envelopes prepared by an independent researcher who was not involved in recruitment or assessment. The allocation was revealed only after the baseline assessment. Baseline, post‐intervention, and follow‐up assessments are conducted by blinded outcome assessors, with different assessors assigned to each group. Intervention delivery and KT application are performed by separate therapists who are not involved in outcome assessments. The statistician will remain blinded to group allocation until the analysis is complete. Due to the nature of the intervention, participant and therapist blinding was not possible. The success of blinding will be evaluated after the study concludes.

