### Outcome Measurements

2.6

Outcome measures included sociodemographic information such as gender, body mass index (BMI), duration and severity of symptoms, radiological findings, comorbidities assessed using the Charlson Comorbidity Index (CCI), history of falls in the past year, physical activity, and other factors relevant to KOA. Primary outcomes focus on pain and functional status, while secondary outcomes include lower‐limb‐specific muscle strength, knee ROM, and functional mobility. Questionnaires were initially developed in English and then translated and back‐translated into Bengali by a bilingual researcher to ensure accuracy and consistency. All outcomes are planned to be assessed at baseline, post‐intervention (8 weeks), and follow‐up (6 months) using questionnaires and clinical examinations, with measurements conducted by trained, blinded assessors.

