##### Pressure Pain Threshold (PPT)

2.6.1.2

PPT of the affected knee joint is being assessed using a handheld digital pressure algometer (FPK 20, Wagner Instruments, USA), a validated method for PPT assessment in KOA. Measurements are taken at the most tender site associated with KOA, recorded three times at 30‐s intervals, and averaged for analysis (ICC = 0.91) [24].

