##### Muscle Strength

2.6.2.1

Lower‐limb muscle strength is being evaluated using a modified sphygmomanometer (Tycos model DS44, NY, USA) that measures pressure from 0 to 300 mmHg, given its feasibility and cost‐effectiveness. This method is a validated, reliable, and clinically acceptable tool for measuring strength. Muscle strength in knee flexion and extension is being evaluated, as these have shown good reliability in previous research (ICC = 0.80–0.99) [26].

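### Outcome assessors are assigned by treatment group, so assessor is nested in arm; this weakens the assessor-blinding claim and conflicts with the stated timing of allocation disclosure

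*Protocol article*

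**What the plan says.** Protocol article, section 2.4 (Randomization and Blinding), covers baseline, 8 weeks and 6 months in one sentence: "assessments are conducted by blinded outcome assessors, with different assessors assigned to each group". The same section says of timing: "The allocation was revealed only after the baseline assessment". It adds that "participant and therapist blinding was not possible", and that the success of blinding will be evaluated once the study ends. Treating therapists are dealt with in a separate sentence, which keeps them out of outcome assessment.

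Section 2.6 (Outcome Measurements) repeats the blinding claim, "with measurements conducted by trained, blinded assessors", without saying that any assessor sees both arms. The title calls the trial assessor-blinded, and the Discussion lists assessor blinding among its strengths.

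Several outcomes depend on the examiner. For pressure pain threshold, a primary outcome taken with a handheld algometer, "Measurements are taken at the most tender site associated with KOA". Among the secondary outcomes, "muscle strength is being evaluated using a modified sphygmomanometer", range of motion is read from a goniometer and TUG is timed.

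Section 2.8 plans a repeated-measures ANOVA with group, time and group × time, plus between-group mean differences with 95% confidence intervals. It names no assessor factor and does not say whether those differences are in change or in single-visit values.

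**The concern.** Three things follow from the assignment rule as worded.

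1. **Confounding.** If one set of assessors measures the KT arm and another the sham arm, any systematic difference in technique (algometer pressure rate, goniometer placement, encouragement during strength testing) lies in the same direction as the treatment contrast. An assessor term in the model could not separate the two.
2. **Blinding.** An assessor who sees one arm knows that all their participants have the same allocation. Participants know their own treatment, so one comment can disclose it for that assessor's whole list.
3. **Contradiction.** Choosing the baseline assessor by group requires someone to know the group before baseline, yet disclosure is said to come afterwards.

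At stake are the feature on which the trial's title rests and the interpretation of one primary and three secondary outcomes.

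**Working it through.** **Reading the clause.** Throughout the article, group means treatment arm (for example, the per-group sample size in section 2.7). Because therapists have their own sentence, the clause does not read naturally as saying only that assessors are not therapists. Nothing elsewhere describes assessors who see both arms.

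**Where an offset goes.** Let D1 and D2 be the difference between the two assessor sets (KT-arm set minus sham-arm set) at baseline and at a later visit, and let δ be the true treatment effect at the later visit.

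- Single-visit difference: δ + D2.
- Group × time (difference in change): δ + (D2 − D1).
- Difference adjusted for baseline with slope β: δ + D2 − β·D1.

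The consequences are:

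| Situation | Single visit | Change (group × time) | Baseline-adjusted |
|---|---|---|---|
| Same group-specific assessors at every visit, constant offset (D1 = D2 = D) | biased by D | unbiased | biased by (1 − β)D |
| Same assessors, with drift or expectation effects (D2 ≠ D1) | biased by D2 | biased by D2 − D1 | biased by D2 − βD1 |
| Group-specific assessors only after baseline (D1 = 0) | biased by D2 | biased by D2 | biased by D2 |

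The group main effect, which section 2.8 also examines, does not benefit from the cancellation in the first row.

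**Size, as an illustration.** The documents give no figure for assessor effects, so there is none to reproduce. The inputs are:

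- 40 per arm, from section 2.7: 34/(1 − 0.15) = 40. Section 2.8 analyses everyone randomized.
- Two-sided α = 0.05, from section 2.8.
- Offset b between the assessor sets, in SD units: assumed, 0.1 to 0.3.

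For one two-sample comparison with no true effect, the standard error is √(2/40) = 0.2236 SD. The noncentrality is b·√(40/2) = 4.472·b, with 78 degrees of freedom. Type I error is the probability that a noncentral t exceeds the two-sided 5% critical value in either tail.

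| Assumed offset b | Noncentrality | Two-sided type I error |
|---|---|---|
| 0 | 0 | 0.050 |
| 0.1 | 0.447 | 0.073 |
| 0.2 | 0.894 | 0.143 |
| 0.3 | 1.342 | 0.263 |

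An offset can also hide a benefit. With the planning effect of 0.61 SD and an offset of 0.2 SD against it, two-sided power at 40 per arm falls from 0.77 to 0.44.

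These figures apply to a single post-treatment comparison. They carry over to group × time only in the third situation of the first table, with b expressed in SDs of the change score.

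**Timing contradiction.** The assessor sentence in section 2.4 names baseline explicitly. If baseline assessors really were chosen by group, allocation was known to someone beforehand. If they were not, the clause is wrong for baseline and the third situation applies. The document does not allow the reader to tell which.

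**The case against.** The strongest reply is that confounding and the baseline contradiction cannot both apply in full. If the rule covers baseline and the same people do every visit, a constant offset drops out of group × time. If it starts later, the contradiction with allocation timing disappears. This is right, and it means that the claim that no analysis can help goes too far. Each branch nevertheless leaves a problem: drift, expectation and early knowledge of allocation in the first, and direct bias of group × time in the second.

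Three stronger readings are tempting but not supported.

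- A reader might infer that assessors know which treatment their participants receive. The rule shows only that their participants share an arm. Both arms wear tape and do the same exercises, assessors are trained, and blinding success will be evaluated. The weakness is that blinding is fragile.
- A reader might take 1 − 0.91 = 9% from the ICC quoted for pressure pain threshold as the assessors' share of variance. With one assessor per arm and 34 per arm, a share of 2% to 9% would give a type I error of about 13% to 35%. The type of ICC is not stated, 1 − ICC also contains random error, the number of assessors is not given, and the calculation describes one unadjusted comparison, not the planned group × time test.
- A reader might want a sensitivity analysis that excludes everyone assessed under the rule. Completion, including the 6-month visit, is expected by December 2026. Counting six months from baseline, the last baseline falls by about the end of June 2026, before the article's September 2026 date. Section 3 says that no outcome data have been collected, so the status is unclear, but such an analysis could leave few or no participants.

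VAS and WOMAC are self-reported, so two of the three primary outcomes are less exposed.

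**Conclusion.** The point holds. As written, section 2.4 nests assessor in arm, makes assessor blinding fragile and conflicts with its own statement on when allocation was disclosed. The examiner-dependent outcomes may be biased, in an unknown direction; of these only pressure pain threshold is primary. A constant offset is harmless to group × time if the same assessors do all visits. It does not cancel in single-visit comparisons or in the group main effect.

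The size is not known. For an assumed offset of 0.1 to 0.3 SD in a single post-treatment comparison with 40 per arm, type I error would be about 7% to 26% instead of 5%. The nesting and the contradiction follow from the wording and need no assumption about size.

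**What to change.** - Delete the clause "with different assessors assigned to each group" and reconcile the sentence with the stated timing of allocation disclosure. If it was meant only to say that assessors are not the treating therapists, reword it to say so.
- For any participant not yet enrolled, assign the existing assessors by branch or rota, independently of allocation, so that each sees both arms. Keep the same assessor for a participant at all visits.
- For participants already assessed under the group-specific rule, state which assessors measured which arm at which visit, and record assessor ID.
- Choose assessors for their remaining visits with the baseline assessor in mind. A switch part-way removes the cancellation of a constant offset.
- Base between-group inference on change or baseline-adjusted analyses. Change removes a constant offset fully; baseline adjustment removes only the fraction β. Neither helps if group-specific assessors began after baseline.
- Report the assessor–arm confounding as a limitation on the assessor-blinded claim. Add a sensitivity analysis by assessment scheme only if enough participants were assessed by assessors who saw both arms.

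The cost is a protocol amendment, a rota change where enrolment is still open, and record-keeping. Staffing is not described, so whether the rota fits current staff is for the trial team to confirm. If the sentence is merely misworded, the cost is a correction to the text. Bias already in completed visits can be disclosed and partly reduced in analysis, but not fully removed.

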### Interventions

2.5

All intervention sessions are conducted by experienced, qualified physiotherapists who received training prior to the study and were provided with treatment manuals and checklists to ensure adherence. Regardless of group assignment, all participants receive usual care at the physiotherapy clinics, which includes education on joint protection, advice on activity modification, and general lifestyle recommendations.

Between baseline and the 8 weeks post‐intervention, participants assigned to the experimental group receive a supervised exercise program combining NCE and KT. Each week comprises three face‐to‐face sessions of approximately 60 min, totaling 24 sessions over the intervention period. Sessions begin with a 10‐min warm‐up (ergometer cycling, treadmill walking, or stepper), followed by NCE, including quadriceps and hamstring strengthening, lunging, pelvic tilting, step‐ups, squatting, weight shifting, mini‐trampoline activities, limping cross, cloth under foot, kettlebell swings, side‐lying jumping jacks, elastic band exercises, and gait training. Exercises progress through three levels, with each performed in 1–3 sets of 15 repetitions. Sessions conclude with a 10‐min cool‐down period consisting of alignment‐focused walking and stretching of the lower extremity muscles. Table 2 provides a clear and detailed description of the NCE protocol [15, 21].

**Table 2 hsr273125-tbl-0002:** Neuromuscular control exercise (NCE) protocol.

Exercise component	Exercise/activity	Purpose and key features	Dose/progression
Warm‐up	Cycling, treadmill walking, or stepper	Low‐intensity whole‐body and lower‐limb warm‐up	10 min; modality selected according to participant tolerance
Muscle strengthening	Quadriceps and hamstring strengthening	Improve lower‐limb muscle strength and neuromuscular control	1–3 sets × 15 repetitions; progress through 3 predefined levels
Functional movement	Squatting	Controlled hip and knee flexion–extension with emphasis on lower‐limb alignment	1–3 sets × 15 repetitions; difficulty progress according to performance
Functional loading	Step‐ups	Improve controlled weight acceptance and lower‐limb loading	1–3 sets × 15 repetitions; progress according to functional capacity
Dynamic postural control	Multidirectional weight shifting	Improve controlled weight transfer and postural stability	1–3 sets × 15 repetitions; progress from basic to dynamic loading
Resistance control	Elastic‐band exercises	Improve resisted lower‐limb movement and neuromuscular control	1–3 sets × 15 repetitions; resistance progress as tolerated
Dynamic coordination	Mini‐trampoline activities, limping cross, cloth‐under‐foot exercise, kettlebell swings, and side‐lying jumping jacks	Enhance dynamic balance, coordination, lower‐limb control, and functional movement	1–3 sets × 15 repetitions; progress through 3 predefined levels
Gait training	Alignment‐focused gait training	Promote controlled gait mechanics and lower‐limb alignment	Protocolized; progress according to movement quality and tolerance
Cool‐down	Alignment‐focused walking and lower‐extremity stretching	Facilitate recovery and maintain lower‐limb flexibility	10 min

*Note:* The NCE program is being delivered three times weekly for 8 weeks (24 sessions), with each session lasting approximately 60 min.

KT is being administered three times weekly over 8 weeks. Before the application, the skin is being cleansed, and participants are being positioned side‐lying with the hip extended and the knee flexed at 60°. An I‐shaped tape is being applied from the rectus femoris origin, with a Y‐shaped tape applied proximal to the superior border of the patella. The tape base is being applied without tension, while the segment directed toward the superior patella is being stretched by approximately 40%. Therapists are receiving standardized training to achieve the target stretch using manufacturer‐recommended reference markers and pre‐measured tape lengths. The tape is being removed after 48 h, and skin sensitivity is being monitored at each reapplication [4, 22].

Participants assigned to the control group are performing the same NCE protocol with sham KT. They are attending three supervised sessions per week for 8 weeks (24 sessions in total), with the same warm‐up, progression model, and cool‐down procedures as the experimental group. Exercise modifications are made when necessary to accommodate individual tolerance while maintaining overall protocol consistency. Sham KT is applied at the same frequency as KT, without stretching and with the knee extended. Any protocol deviations are documented for reporting in the final results. Participant tolerance and adverse events are monitored throughout the intervention using individual monitoring sheets to ensure safety.

### Outcome Measurements

2.6

Outcome measures included sociodemographic information such as gender, body mass index (BMI), duration and severity of symptoms, radiological findings, comorbidities assessed using the Charlson Comorbidity Index (CCI), history of falls in the past year, physical activity, and other factors relevant to KOA. Primary outcomes focus on pain and functional status, while secondary outcomes include lower‐limb‐specific muscle strength, knee ROM, and functional mobility. Questionnaires were initially developed in English and then translated and back‐translated into Bengali by a bilingual researcher to ensure accuracy and consistency. All outcomes are planned to be assessed at baseline, post‐intervention (8 weeks), and follow‐up (6 months) using questionnaires and clinical examinations, with measurements conducted by trained, blinded assessors.

#### Primary Outcomes

2.6.1

##### Visual Analog Scale (VAS)

2.6.1.1

Pain intensity is being assessed using a simple 10 cm VAS, a widely used tool for measuring pain. It features a 10 cm horizontal line, with 0 representing “*no pain*” and 10 indicating “*severe pain*.” The VAS has shown excellent reliability in measuring KOA pain, with an ICC of 0.97 [23].

##### Pressure Pain Threshold (PPT)

2.6.1.2

PPT of the affected knee joint is being assessed using a handheld digital pressure algometer (FPK 20, Wagner Instruments, USA), a validated method for PPT assessment in KOA. Measurements are taken at the most tender site associated with KOA, recorded three times at 30‐s intervals, and averaged for analysis (ICC = 0.91) [24].

##### Functional Status

2.6.1.3

Functional status is being assessed using the Western Ontario and McMaster Universities Osteoarthritis Index (WOMAC), a validated instrument for assessing KOA. It includes 24 items across pain (ICC = 0.86), stiffness (ICC = 0.68), and physical function (ICC = 0.89), with sub‐scores of pain (0–20), stiffness (0–8), and physical function (0–68), totaling 96 [25].

#### Secondary Outcomes

2.6.2

##### Muscle Strength

2.6.2.1

Lower‐limb muscle strength is being evaluated using a modified sphygmomanometer (Tycos model DS44, NY, USA) that measures pressure from 0 to 300 mmHg, given its feasibility and cost‐effectiveness. This method is a validated, reliable, and clinically acceptable tool for measuring strength. Muscle strength in knee flexion and extension is being evaluated, as these have shown good reliability in previous research (ICC = 0.80–0.99) [26].

##### Range of Motion

2.6.2.2

Knee joint ROM is being assessed utilizing a standard goniometer, a valid tool in clinical research and physiotherapy practice. Knee flexion–extension ROM is being assessed, a measure that has demonstrated excellent reliability in previous research (ICC = 0.99) [27].

##### Timed UP and Go Test (TUG)

2.6.2.3

The TUG test is being used to evaluate functional mobility. The TUG records the time taken to rise from an armchair, walk 3 meters, and return to a fully seated position. Time is being measured in seconds, and a duration exceeding 12 s indicates a fall risk. This is a valid and reliable testing procedure for mobility impairments and falls in KOA patients (ICC = 0.96) [28].

### Sample Size Calculation

2.7

G*Power, version 3.1.9.7 (University of Kiel, Kiel, Germany), was used to determine the required sample size for this study. The calculation indicates that a total of 68 participants are required, with an effect size (ES) of 0.61 for the functional outcomes, an *α* level of 0.05, and a power of 0.80 [29]. Therefore, each group requires 34 participants. After accounting for a 15% dropout rate, the number of participants in each group is increased to 40, resulting in a final estimated total of 80 participants.

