### Statistical Analysis

2.8

All statistical analyses will be performed using SPSS (Statistical Package for the Social Sciences), version 25 (IBM Corp., Armonk, NY, USA). Descriptive statistics will be presented as frequencies, percentages, means, and standard deviations, as appropriate. For between‐group comparisons of baseline characteristics, independent‐samples *t* tests will be used for continuous variables, and Pearson's Chi‐square (*χ*
^2^) tests will be used for categorical variables. Changes in outcome measures across the three assessment time points will be evaluated using repeated‐measures analysis of variance, with group, time, and group × time interaction effects examined to assess differences in trajectories between the intervention groups. Where appropriate, post hoc comparisons will be performed with adjustment for multiple comparisons. ESs will be estimated using partial eta squared (ηp^2^) for the repeated‐measures analyses and Cohen's d for pairwise comparisons, with Cohen's d values of 0.20, 0.50, and 0.80 interpreted as small, moderate, and large effects, respectively. Between‐group mean differences will be reported with corresponding 95% confidence intervals (CIs) to enhance the precision and clinical interpretability of the estimates. All analyses will follow the intention‐to‐treat principle, including all randomized participants in the analysis according to their assigned groups. Missing data will be addressed using multiple imputation under a missing‐at‐random assumption. A two‐sided *p*‐value of < 0.05 will be considered statistically significant.

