The study findings could significantly benefit KOA management practice by endorsing a safe, cost‐effective, and easily implementable intervention that requires neither sophisticated equipment nor extensive financial investment. The strengths of this study include its multicenter design, assessor blinding, adequate sample size, standardized intervention protocol, and long‐term follow‐up. These methodological features enhance the internal validity and reliability of the results. However, some limitations should be considered. The study is being conducted in a Bangladeshi population, which may limit the generalizability of the findings to other populations and healthcare settings. Variations in exercise adherence and follow‐up participation may influence the study outcomes. Although adverse events are expected to be minimal, some participants may experience discomfort or delayed‐onset muscle soreness, which may affect their adherence to or engagement with the intervention. Furthermore, as both groups are receiving the same NCE program, the study is primarily designed to determine the additional effect of KT rather than the independent effects of KT or NCE alone. Future research should investigate the long‐term sustainability, cost‐effectiveness, and cross‐cultural applicability of KT combined with NCE or other exercise interventions, while incorporating advanced radiological imaging to assess structural changes across different stages of KOA.

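### The 34 per group matches a one-sided t test at d = 0.61, but the plan tests two-sided, where an unadjusted comparison has about 70% power, not 80%

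*Protocol article*

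**What the plan says.** Section 2.7 (Sample Size Calculation) cites G*Power 3.1.9.7 and gives the total, effect size, alpha and power: "The calculation indicates that a total of 68 participants are required, with an effect size (ES) of 0.61 for the functional outcomes", with an alpha "level of 0.05, and a power of 0.80". It continues: "Therefore, each group requires 34 participants". An allowance of 15% for dropout raises this to 40 per group, 80 in total. The section does not name the test, say whether alpha is one- or two-sided, or say which kind of effect size 0.61 is.

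Section 2.8 (Statistical Analysis) plans repeated-measures ANOVA over three time points and fixes the criterion: "A two‐sided *p*‐value of < 0.05 will be considered statistically significant". Section 2.4 gives 1:1 allocation. The Discussion lists "multicenter design, assessor blinding, adequate sample size" among the strengths of the trial.

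**The concern.** A sample size and the test it serves should use the same error rate. Here the published inputs lead to 34 per group under the usual two-group calculation only if all 5% of alpha is put in one tail, whereas the plan splits it over two.

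The stake is how the result will be read. The Introduction calls the existing evidence on taping inconclusive, so a null result is a real possibility. A reader told that the trial had 80% power and an adequate sample would take such a result as fairly strong evidence against an effect of 0.61. If the chance of missing that effect is nearer 30% than 20%, the same result says less. The type I error rate is not affected, and no estimate is biased.

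**Working it through.** **Inputs.** Effect size 0.61, alpha 0.05, power 0.80, 34 per group, dropout 15% (section 2.7); 1:1 allocation (section 2.4); two-sided criterion (section 2.8). Assumption: 0.61 is Cohen's d, since the type is not stated.

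**Method.** Two-sample t test with n per group: degrees of freedom 2n − 2, noncentrality d × √(n/2). Power is the probability that a noncentral t variable exceeds the critical value (in either direction for the two-sided test).

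**Step 1: reproduce the plan's figure.** At n = 34 there are 66 degrees of freedom and the noncentrality is 0.61 × √17 = 2.515. The one-sided 5% critical value is 1.668.
- n = 33: power 0.790
- n = 34: power 0.801

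The smallest n reaching 0.80 is therefore 34 per group, 68 in total, exactly as stated. Dropout: 34 / (1 − 0.15) = 40 per group, 80 in total, which is also correct.

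**Step 2: repeat with the planned two-sided criterion.** The critical value at 66 degrees of freedom rises to 1.997.

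| n per group | Two-sided power at d = 0.61 |
|---|---|
| 34 (expected completers) | 0.698 |
| 40 (no dropout) | 0.769 |
| 43 | 0.798 |
| 44 | 0.808 |

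The two-sided requirement is 44 per group, 88 in total. With 15% dropout it is 44 / 0.85 = 51.8, so 52 per group, 104 in total. The normal approximation gives much the same: 43 per group, with power 0.711 at 34 and 0.779 at 40.

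**Step 3: the effect the trial can detect.** Solving for two-sided power 0.80 gives d = 0.690 at 34 per group and d = 0.634 at 40 per group.

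**Step 4: other routes to 68.**
- *Repeated-measures ANOVA, between-group effect.* With f = d/2 = 0.305, m measurements and within-person correlation ρ, the noncentrality is λ = N f² m / (1 + (m − 1)ρ), on 1 and N − 2 degrees of freedom. The smallest even N with power 0.80 is 66 at m = 2, ρ = 0.5, and 70 at m = 3, ρ = 0.7. It is exactly 68 for ρ of about 0.52 to 0.56 with two measurements, and about 0.64 to 0.67 with three. Over ρ from 0 to 0.8 the answer runs from 32 to 78.
- *Group × time interaction, f = 0.305.* N is 46 or fewer for ρ from 0 to 0.8, so this does not give 68.
- *0.61 read as Cohen's f.* N is 22 or fewer in every repeated-measures setting tried.
- *Mann-Whitney test.* 36 to 40 per group one-sided and 46 to 50 two-sided, depending on the efficiency assumed; neither gives 34.

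**The case against.** The strongest reply is that the planned analysis is repeated-measures ANOVA, so a t test is the wrong yardstick, and that a two-sided between-group F test can itself give 68. The second part is true, as step 4 shows. A reader might therefore infer too much in saying that 68 can arise only from a one-sided test. Section 2.7 does not state sidedness, so the one-sided reading is an inference from an exact numerical match. What weakens the alternative is that it needs a number of measurements and a correlation, neither of which section 2.7 gives, and that the correlation must fall in a narrow band. The one-sided t test needs no input beyond those published.

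A second reply is that the 70% figure is conditional, and this stands. It applies to an unadjusted comparison of 34 completers per group. Section 2.8 plans to use three time points and all randomized participants, with multiple imputation. A reader might infer that the trial's true power is 70%. The article does not support that: power under the planned repeated-measures analysis depends on a correlation it does not give, and could be below or above 80%.

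A third reply is that a journal article may leave such detail to the full protocol. That would answer a complaint of omission. Here the effect size, alpha, power, N and a two-sided criterion are all published, and under the standard two-group calculation they disagree.

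**Conclusion.** The point holds in this form: on the inputs that section 2.7 states, 68 participants do not give 80% power for the two-sided test in section 2.8. The number equals the one-sided two-sample answer exactly; the two-sided answer is 88. Unadjusted two-sided power at d = 0.61 is about 70% at 34 per group and about 77% at 40 per group, and 80% power at 34 per group corresponds to d of about 0.69.

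This rests on 0.61 being Cohen's d and on an unadjusted two-group comparison. One-sided sizing is the most plausible explanation, but it is not proven. Nothing else in the article reconciles the two sections. If a repeated-measures calculation was used, its inputs would settle the matter.

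**What to change.** Keep 80 participants and the two-sided test.

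1. In section 2.7, name the test, its sidedness and the type of effect size.
2. Restate the power there. For example: for an unadjusted two-sided 0.05 comparison and d = 0.61, power is about 70% with 34 evaluable participants per group and about 77% with 40; with 34 per group, 80% power corresponds to d of about 0.69.
3. If a repeated-measures calculation produced 68, report that instead, with the effect tested, the number of measurements and the within-person correlation assumed.
4. In the Discussion, qualify the sample-size claim so that it agrees with section 2.7.

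The cost is rewording in two sections, best done before the results are analysed. No participants are added and no trial procedure changes. Unless item 3 applies, the stated power becomes less favourable.
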